### Randomization

GPs will be cluster randomized for the study. The clusters of GPs will be randomized, in a 1:1 ratio, to either the Coordinated-care or the Usual-care group. The randomization will be stratified by the geographical region related to the University Department of General Practice (Angers, Nantes, Rennes, and Nice). The study plans to enroll 20 GP clusters distributed as follows: 10 clusters for the Department of General Medicine attached to Angers (5:5), 4 for each of those attached to Nantes (2:2) and Rennes (2:2), and 2 for that attached to Nice (1:1). The randomization of the clusters for the Department of General Medicine attached to Angers (10 clusters) will also be stratified by the time of study initiation, since the synchronous initiation of the clusters in Angers is not feasible. The randomization will be performed by the Biostatistical Department of the University Hospital Center (“CHU”) at Angers. All patients followed up in the same cluster will be allocated the same group as their GP.

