### Statistics

Quantitative data will be presented as means with standard deviations and will be compared using Mann–Whitney tests. Qualitative data will be presented as numbers with percentages and compared using Fisher’s exact tests.

For the primary objective, the proportion of patients that have an improved (lower score) of at least 4 points, in the RMDQ, at 12 months after enrollment will be compared in the study groups. The analysis will be performed using a multilevel logistic mixed model that will allow the clustering effect to be considered as random.

Similarly, the secondary outcome measures with binary outcomes compared between the study groups (e.g., the proportion of patients that improved by at least 2 points on the numerical pain scale at 12 months) will be analyzed by multilevel logistic mixed regression models.

Secondary outcome measures assessing changes in a quantitative parameter over time (e.g., the evolution of the RMDQ scores measured at baseline and then at 3, 6, and 12 months after enrollment) will be analyzed using linear multilevel mixed regression models. The individual effect will be included in the cluster effect. Time will be considered as qualitative variables with a varying number of modalities, e.g., 4 modalities for outcomes assessed at baseline, and then at 3, 6, and 12 months, and 3 modalities for outcomes assessed at baseline, and then at 3 and 6 months. The effect of the intervention will be evaluated by including an interaction between the variables for time and for the study group. The effect of the intervention will be assessed at each time point. The increased alpha-risk, due to multiple analyses, will be accounted for using the Bonferroni correction.

For these various multilevel models, the variance–covariance matrices will be considered as unstructured. Missing data will be treated using a set of 10 multiple imputations based on chained equations (38, 39). The analyses will be performed bilaterally with the alpha-risk set at 5%, except in cases where the Bonferroni correction was used. The data will be analyzed on an intent-to-treat basis. Thus, all patients with data will be included in the analysis unless they specifically indicate that they do not want their data analyzed.

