GPs in the interventional group may preferentially include patients with severe LBP instead of enrolling all eligible patients if they consider the intervention to be better than usual care, and that this improved care may benefit patients with severe LBP more than patients with less severe LBP. This phenomenon may also occur in the control group, where GPs may be reluctant to suggest study participation because of the protocol’s constraints, to patients with non-severe LBP. We have examined this issue and will address this by providing continuous support for GPs during the study. Where a significant difference between groups in terms of patient’s LBP status at baseline is observed, we planned to adjust analyses to limit the impact of this bias on the results.

Most studies that have assessed the clinical evolution of LBP have used either pain, incapacity, and/or returning to work to measure the effectiveness of interventions (33, 49). However, from a patient’s perspective, reduced LBP is mainly comprised of three dimensions: attenuated pain, improved functional capacity, and combined with an acceptable quality of life, which includes the capacity to work (24). In our study, we chose perceived disability, considered by patients to be of utmost importance, as our primary outcome measure. However, we have included several secondary outcome measures, including measures to assess pain, quality of life, and the patients’ occupational status—other important facets of LBP.

Currently, in France, primary healthcare professionals, working in the same geographical region, are encouraged to group together in multidisciplinary practices. Our study is consistent with this evolution of primary healthcare, evaluating a coordinated strategy composed of a multidisciplinary team. Moreover, our study allows healthcare professionals in each region to form networks that hopefully will persist after the study has been completed. Consequently, we will cluster randomized GPs in the same region to promote local cooperation among professionals.

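### The described models name neither stratification factor; if region or Angers start time predicts outcome, the standard error is overstated, and correcting it needs a small-sample method

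*Protocol article*

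**What the plan says.** **Randomization section.** "The randomization will be stratified by the geographical region related to the University Department of General Practice". The 20 clusters are split 10, 4, 4 and 2 over Angers, Nantes, Rennes and Nice, with equal numbers per arm in each region. The Angers clusters "will also be stratified by the time of study initiation, since the synchronous initiation of the clusters in Angers is not feasible". The number of Angers periods is not given.

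**Statistics section.** On the primary outcome: "The analysis will be performed using a multilevel logistic mixed model that will allow the clustering effect to be considered as random". Binary secondary outcomes "will be analyzed by multilevel logistic mixed regression models". For repeated quantitative outcomes, patients are nested in clusters, time is categorical, and "The effect of the intervention will be evaluated by including an interaction between the variables for time and for the study group". The section also fixes the covariance structure, the Bonferroni correction, the number of imputations and two-sided testing. No model names region or initiation time.

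**Discussion section.** Adjustment appears only conditionally. If the groups differ at baseline in LBP status, "we planned to adjust analyses to limit the impact of this bias on the results"; a similar provision covers baseline levels of the professionals' beliefs score if needed.

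**The concern.** Balanced stratification removes differences between regions, and between Angers periods, from the true sampling error of the treatment contrast. A model with only a random cluster effect does not know this. It counts those differences as ordinary between-cluster variation, so the reported standard error can exceed the true one. Confidence intervals are then too wide, the test falls below its nominal level, and part of what the stratification was meant to deliver is lost. The strata are also the one set of covariates known before any data exist, whereas the adjustments that the article does mention depend on observed imbalance.

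**Working it through.** **Inputs from the article (Sample size and Randomization sections).** Response 50% vs 70%; two-sided alpha 0.05; power 80%; 25 patients per cluster; coefficient of variation of cluster size 0.2 (the following text prints 0.02; 0.2 is used here); ICC 0.03; attrition 20%; clusters 10/4/4/2.

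**Assumptions not in the article.** The share of between-cluster variance carried by the strata (0, 25, 50 or 75%), and two Angers periods of 4 and 6 clusters.

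**1. The plan's own figure.** Two proportions without clustering: 93 per arm. Design effect = 1 + ((1 + 0.2²) × 25 − 1) × 0.03 = 1.75. Then 93 × 1.75 = 162.8; 162.8 / 0.8 = 203.4; 203.4 / 25 = 8.14, so 9 clusters, plus 1 for the small number of clusters = 10 per arm. The stated 20 clusters and 500 patients are reproduced. The calculation takes no credit for stratification.

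**2. Power of the planned design.** With 20 analysed per cluster, the design effect is 1 + (1.04 × 20 − 1) × 0.03 = 1.594, and the effective size is 200 / 1.594 = 125.5 per arm. Power is 90.3% (normal), 87.7% (t, 18 df), 87.0% (t, 15 df, region added) and 85.2% (t, 11 df, if region and Angers periods made 8 strata).

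**3. Hand check of the standard error, region only.** In units of p(1−p), the variance of a cluster mean is 0.03 + 0.97/20 = 0.0785, of which 0.03 / 0.0785 = 38% is between clusters.
- If regions carry half of the 0.03, the variance relevant to the stratified comparison is 0.015 + 0.0485 = 0.0635.
- The unadjusted residual variance also picks up the region part, multiplied by (20 − (10² + 4² + 4² + 2²)/20) / 18 = 13.2 / 18 = 0.733. It is 0.0635 + 0.733 × 0.015 = 0.0745.
- Ratio of standard errors: √(0.0745 / 0.0635) = 1.083, so about 8% too large.
- At a quarter share: √(0.0765 / 0.0710) = 1.038, so about 4%.
- At ICC 0.01, the median that the article cites: √(0.0582 / 0.0545) = 1.033 at half share, so about 3%.

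**4. Simulation of the logistic mixed model.** 4,000 trials per scenario, maximum likelihood, about 20 analysed per cluster. At a true 5%, the Monte Carlo standard error is √(0.05 × 0.95 / 4000) = 0.34 points. SEs are for the log odds ratio under the null; "with strata" means region plus Angers period.

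| Stratum share | Model SE / true SE, no strata | Type I, no strata (normal / t) | Type I, with strata (normal / t) | Power, without / with strata (t) |
|---|---|---|---|---|
| 0% | 0.248 / 0.261 | 6.8% / 4.9% | 9.4% / 6.5% | 88.0% / 90.6% |
| 25% | 0.250 / 0.252 | 6.5% / 4.9% | 9.4% / 6.8% | 87.6% / 91.7% |
| 50% | 0.251 / 0.233 | 4.2% / 3.2% | 7.3% / 5.0% | 89.3% / 94.1% |
| 75% | 0.253 / 0.220 | 2.9% / 2.2% | 6.3% / 4.4% | 90.7% / 95.5% |

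At half share the overstatement is 0.251 / 0.233 = 1.08. The true SE hardly changes when strata are added (0.220 vs 0.222 at 75%). The power differences in the last column are not pure gain: 90.6 − 88.0 = 2.6 points appear even where strata explain nothing, which is excess type I error.

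**5. Simulation of a cluster-level analysis, t reference.** Without strata, type I error is 5.0%, 4.1% and 3.2% at shares of 0, 25 and 50%, and the SE is about 9% too large at 50%. With region and period it stays at 4.9 to 5.1%. Power changes by about −1 to +3 points.

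**The case against.** The strongest objection is that silence is not exclusion. This is a condensed article, its analysis plan is not shown, and the sentence on the primary model describes only the random part without even naming the treatment term. A covariate list is often left to the analysis plan. This stands to the extent that nobody can say the strata will be left out. It does not dispose of the point: the article fixes many finer details of the same models and discusses adjustment, yet only on condition of observed imbalance.

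Stronger readings are tempting, and the documents do not support them:
- **That the test is conservative.** This depends on a between-stratum variance that the article does not give. At a share of 25% or less, the unadjusted logistic model is near nominal with a t reference (4.9%) and slightly liberal with a normal one (6.5 to 6.8%), because there are only 20 clusters.
- **That precision is wasted.** The balanced allocation already gives the estimator its precision; only the reported standard error is affected.
- **That between-cluster variance dominates.** It is about 38% of the variance of a cluster mean at ICC 0.03.
- **That the trial is underpowered.** Power without strata is about 88 to 91% (t), above the planned 80%.
- **That adding the terms is harmless.** With an ordinary Wald test it would replace a possible mild conservatism by a clear excess of type I error.

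**Conclusion.** The point holds as one of efficiency and specification, not of validity. Randomization is stratified by two factors that no described model names. If the strata carry half of the between-cluster variance at ICC 0.03, the standard error is about 8 to 9% too large and the type I error about 3 to 4%. At a quarter share the effect is small, and with no stratum effect it vanishes. In an analysis that holds its level, the power lost is about 3 points at half share; the larger differences in the logistic simulation (up to 4.8 points) cannot be read at face value. The size rests on the assumed stratum shares, the assumed two Angers periods and the planned ICC; at ICC 0.01 it shrinks to about 3% of the standard error at half share. The sample size of 500 does not change.

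**What to change.** State in the protocol or analysis plan that region (four levels) and, within Angers, initiation period enter as fixed effects in the primary model and in the between-arm models of the secondary patient outcomes, and give the number of periods. If they are to be left out, say why.

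Name a small-sample method in the same sentence, for example a t reference with between-cluster degrees of freedom or a stratified cluster-level analysis. In the checks above, the t reference brought the adjusted logistic model to 4.4 to 6.8%, while the stratified cluster-level analysis held 4.9 to 5.1%. If the mixed model is kept as primary, its chosen correction should therefore be verified by simulation on the 10/4/4/2 layout.

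The cost is a short text change and some between-cluster degrees of freedom: 3 for region plus those for the Angers periods. If the strata explain nothing, power falls from 87.7% to 87.0% with region alone, by about 1 point with few periods, and to 85.2% with 8 strata in all. With 41 patients enrolled at the status date given in the article, enrollment was still at an early stage when it was published.

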### Interventions

Prior to the study, all healthcare professionals (GPs and associated physiotherapists) in the clusters allocated to the Coordinated-care group will undergo a 2-session training for the study interventions. The training sessions will be performed within each of the 10 clusters. Each training will be comprised of two sessions separated by a 2-to-4-week time interval. The first 90-min training session will focus on three blocks: the factors that may influence the evolution and treatment of LBP, the French recommendations that promote active LBP management with therapeutic education (13), and the tools available for maintaining employment in patients with LBP. This first session will be performed autonomously by GPs and physiotherapists, guided by a video. The professionals will be asked to produce a written summary of their exchanges on each block. During the 2–4-week interval between the training sessions, the GPs and physiotherapists will be invited to complete auto-observation questionnaires concerning any patients with LBP that consult them. The second session will consist of a three-and-half-hour in-person training, at each cluster’s location, by the clinical training team: made up of the same doctor and physiotherapist. In addition, the clinical training team will systematically invite a local OP to this second session. The session will combine formal presentations related to each interventional component (psychosocial factors in LBP, active exercise reeducation program for patients with LBP, and the tools to maintain employment). The training session will also include several periods of time for the health care professionals to exchange their clinical experiences, and to propose ways to evolve their practices to incorporate the elements associated with the study intervention. During the session there will be a final sequence focusing on interprofessional collaboration, during which the healthcare professionals will decide on the modalities for collaboration to be implemented in the study.

The aim of the training will be for the healthcare professional to appropriate the concepts, tools, and interventions applied during the study. During the training, healthcare professionals will also discuss various aspects of healthcare including care providers, resources offered in the region, as well as potential barriers to collaboration, and how to overcome these barriers.

Healthcare professionals in clusters allocated Usual-care received no study-specific clinical training.

The primary care interventional components in the Coordinated-care group will be as follows:

Exploration and management of psychosocial factors

Healthcare professionals (GPs and physiotherapists) will be asked to explore, during their consultations, various psychosocial factors, including individual psychological, psychiatric, cognitive-behavioral, family factors (usually named as “yellow flags”), socio-economic factors (usually named as “blue flags”), and socio-occupational factors (usually named as “black flags”). The factors impacting the transition from acute to chronic LBP and the appropriate clinical care will be discussed in detail during the training (4, 10, 14, 15). Furthermore, eligible patients, allocated to the Coordinated-care group will be systematic given the French social security brochure, “I suffer from LBP: what is it and what should I do?” (translated from the French: “Je souffre de lombalgie: de quoi s’agit-il et que faire?”) by their GP (16). The brochure will help to educate the patient concerning the evolution of LBP and to eliminate false beliefs.

During the study, the GP will continue to follow the patients according to the patients’ individual needs and preferences, as assessed by the patients and their GP. The general recommendation will be to perform regular follow-up visits (for example weekly or every 2 weeks, at least during the early phase of medical care, and especially in the case of sick leave) until LBP-related complaints have been resolved. No specific frequency for the consultations will be imposed by the protocol since the overmedicalization of LBP is known to promote the development of chronic LBP (17). In particular, the duration of disability is known to increase with the number of healthcare consultations, with referrals to specialists, and performing early diagnostic imagery (18).

Active exercise reeducation program

Patients in the Coordinated-care group will have access to individual reeducation by a physiotherapist trained for the study. The reeducation will be composed of an intensive exercise rehabilitation program. The program comprises of up to 15 sessions of 1 h, 2–3 times per week and included therapeutic education. This approach is commonly recommended for treating LBP (19), but not frequently implemented (due to limited availability of physiotherapists and/or costs for patients). In clinical trials evaluating the efficacy of these programs, these programs usually last between 8 and 31 h. Depending on the physiotherapist’s assessments during the program and the patient’s needs and preferences, the program can be stopped before the 15^th^ session or can be extended with maintenance therapy sessions.

Use of tools to maintain employment

GPs and physiotherapists in the Coordinated-care group will be trained during the study to use the tools to maintain employment and will be encouraged to implement these tools early during LBP management to prevent prolonged incapacity at work, extended sick leave or even job loss.

GPs and physiotherapists will be asked to systematically inquire about the occupational situation of their patients throughout the study to better appreciate the evolution of the patient’s situation and to adapt the clinical strategy.

The following recommendations and tools, for maintaining employment will be proposed:

✓ GPs and physiotherapists will be requested to systematically refer their patients to either their OP or an occupational nurse (depending on the healthcare organization and the resources available) within 15 days after enrollment.✓ GPs and physiotherapists will be asked to encourage their patients to return to work as early as possible, considering their clinical and occupational situation. Also, health professionals should favor short periods of sick leave, of 1–2 weeks (particularly during the early stages of LBP), instead of long periods. Also, patients will be systematically proposed an appointment with their GP before returning to work.✓ GPs and physiotherapists will be requested to use the tools to help maintain employment available in France in all relevant situations (12). During the study training, GPs will be trained to use the 3 main tools: a visit with the OP before returning to work after a sick leave (referred to as the “pre-return-to-work visit”), a progressive return to work based on part-time work for therapeutic reasons (referred to as “therapeutic part-time work”), and the “recognition of handicapped worker status.” These tools will be discussed in detail, including their usefulness, their limitations, and how to implement them in practice, considering local resources and the healthcare organization.

Increased cooperation among healthcare professionals for a coordinated care for patients

The cooperation between healthcare professionals within a cluster, allocated the study interventions, will be initiated during the study training as an explicit component of the intervention. The cooperation will be facilitated by the proximity of healthcare professionals in the study. At the portion of the training session dedicated to the collaboration between healthcare professionals, time will be allocated for the professionals to discuss obstacles, opportunities for and modalities to collaborate. The use of tools available locally, but underused, including shared information systems and multidisciplinary meetings, will be encouraged for patients included in the study. The GPs will be instructed, with permission from the patient, to provide the physiotherapists not only with the prescription but also the relevant clinical information at the start of treatment. The physiotherapists will be instructed to provide the GP with a final report including an assessment of the patient’s condition once the patient completed the reeducation program. Also, when justified by the patient’s clinical situation, communication between GPs and physiotherapists will be encouraged throughout the reeducation program. Furthermore, the healthcare professionals will be encouraged to correspond or initiate communication with all healthcare professional implicated in the patient’s treatment and return to work, even those not participating in the study. Finally, the following 3 templates for letters will be provided by the research team: a reference letter template from the GP to the physiotherapist, a final report template from the physiotherapist to the GP at the end of reeducation program, and a template from the GP to the OP or occupational nurse. Professionals in the clusters allocated to the Coordinated-care group will be instructed to locally adapt these templates as required and/or to use their own templates.

This multi-faceted study intervention was designed as a coordinated and comprehensive biopsychosocial healthcare strategy. The intervention is fundamentally patient centered: adapted to the needs and preferences of each patient. The healthcare professionals must evaluate the pertinence of each part of intervention according to the patient’s specific situation, and to incorporate the patient’s preferences in the treatment decision, following a shared decision approach. The patient will remain free to accept or not, or to delay, any proposed part of intervention without being excluded from the study.

Patients in clusters allocated usual care are treated according to the GP’s usual practice.

To avoid creating a feeling of injustice in healthcare professionals allocated the non-intervention group and to motivate them to actively participate in the study, the 2-session training will be offered to physicians and physiotherapists of these clusters after the end of the study.

